### Frailty index

The frailty index operationalizes frailty in clinical practice and for research [1, 22]. Frailty index scores are calculated as a ratio of health deficits present to total deficits assessed, with a higher value indicating worse frailty levels. For this study, a multi-item frailty index will be calculated based on a health history questionnaire completed by the patient or care partner (if necessary). The specific health questionnaire includes signs/symptoms, mobility, cognition, mood, quality of life, activities of daily living, and nutrition (Supplemental File 2). Frailty will be determined at admission, each week for 1-month (then monthly thereafter), and at a 1-month post-discharge phone call. In hospitalized older adult patients, a change of 0.03 has been demonstrated to be a clinically meaningful change for frailty index scores [23]. In addition to the changes in the continuous frailty score, we will also examine the proportion of patients whose frailty index changes by 0.03 and 0.10 from admission to discharge; 0.10 is considered a moderate change in the frailty index score [24].

### Secondary outcomes

Hospital length of stay will be determined at hospital discharge. Hospital readmissions within 30 days will be quantified by self-report at the one-month follow up time point after hospital discharge. Falls will be tracked by research assistants during their daily visits and will also be assessed by self-report at the one-month follow up time point after hospital discharge.

The Pictorial Fit-to-Frail Scale will also be conducted as a secondary measure of frailty that is completed independently by the patient (or their care partner if necessary) on admission and prior to discharge [25, 26]. A Comprehensive Geriatric Assessment is a multi-disciplinary diagnostic and treatment process that provides a tool to direct patient care. A physician or trained researcher will conduct this Comprehensive Geriatric Assessment upon admission and discharge. A frailty index can be calculated from a Comprehensive Geriatric Assessment and will be quantified in this study [27]. The following cognitive battery tests will be administered at admission, each week for 1-month (then monthly thereafter), and at a 1-month post-discharge phone call: the Rey Auditory Verbal Learning Test (immediate and delayed), Verbal Fluency, Animal Naming, and Mental Alternation Test [28, 29].

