## Background

Frailty is a state of increased vulnerability to adverse health outcomes, due to the accumulation of health deficits [1]. Hospitalized patients living with frailty have a higher risk for functional decline, new impairments in activities of daily living, a longer hospital stay, hospital readmission, and death [2–4]. The risk of hospital-associated deconditioning may be related to the severity of illness, frailty, and hospital structure/processes of care [5]. In general, hospitalized patients spend > 93% of their time lying in bed awake, even if they can walk independently [6]. This excessive sedentary time puts patients’ in-hospital recovery and post-hospital independence at risk. Sedentary time is characterized by a low energy expenditure (< 1.5 metabolic equivalents of task) during awake hours, while in a seated, reclining, or lying posture [7]. Strategies that help address patients’ excessive time spent in bed may attenuate the accelerated development of frailty that accompanies hospital stays.

Based on thigh-worn inclinometry, hospital inpatients are upright for ~ 50 min/day during their waking hours [8], which is much less than reported values of community dwelling older adults (~ 6 h/day; [9]). Observational data have indicated that older patients who walked at least once/day outside their room during hospitalization had ~ 1.7 days shorter length of hospital stay compared with those who stayed in their room [10]. Greater sedentary time in hospitalised older adults is also associated with greater loss of knee-extension strength [11]. While observational studies support the positive impact of moving more on patient health [8, 10], multiple barriers exist to promoting upright time in a hospital, including fall concerns, pain, and lack of patient motivation [12]. Pragmatic interventional studies are needed to help patients move more and limit their sedentary time to address the health impacts of immobility during a hospital stay.

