### Randomization and blinding

Participants will be randomized into intervention or control by a statistician using an n = 6 block design and stratification by participants’ maximum level of mobility at pre-admission. We will identify the patients’ pre-admission mobility level by asking them or their care partner at admission whether the patient, 1) walked independently (i.e., no walking aid or additional person required), 2) required a walking aid (e.g., walker) but not the assistance of another person, or 3) required the assistance of another person. This blocking and stratified randomization was done using the randomizeR package (v2.0.0) [19] and ensures a close to equal number of participants in each group and that the proportion of patients with the same movement capabilities are distributed evenly into the intervention and control groups. The primary investigator and data collection assessors are blinded to participant group assignment; the data analyst will also be blinded.

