### Intervention group

The intervention group will receive usual care, physical activity monitors (see below for details), and visits from researchers to set daily activity goals and promote movement. Specifically, research assistants (with backgrounds in kinesiology) will visit each patient in the morning and afternoon/evening every day during hospitalization (i.e., 14 times per week) to set a step goal in the morning and check on progress towards this goal later in the day. A white board will be positioned in their room and the specific step goal will be written on it as a target for the patient. A target of up to ~ 20% increase in step counts from the previous day will be initially used. If participants have not achieved their daily goal, feedback will be provided to the patients and patients will be safely mobilized to the maximum level of their ability in the afternoon/evening. While there is a specific step goal, this is not designed to be an all or nothing approach, with the patient encouraged to move to the most of their abilities (e.g., those who are sitting a lot will be encouraged to stand more). Patients who do not meet their target will be encouraged to do whatever is possible within their mobility limits. The research assistants will help facilitate movement and offer going for a brief walk if the patient is interested. The overarching purpose is to promote more movement in an acute care setting to facilitate a more realistic adoption of this intervention into clinical care rather than a pass/fail of specific number of steps increased day-to-day.

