### Control group

Those randomized into the control group will receive usual care and will undergo the same social engagement as the intervention group but without the encouragement to engage in more activity and setting activity goals. The control group will receive brief visits from the research assistants conducting the intervention at the same time they went into the unit to visit intervention participants to ensure consistency of the social engagement aspect between intervention-control groups. This entails brief (< 5 min) small talk as how their day is going, if the monitor is annoying them, etc. White boards with random numbers will be placed in the control group patients’ rooms so that the researchers responsible for conducting health assessments will be blind to group allocation.

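### In-hospital falls are recorded by the unblinded assistants who deliver the intervention, an exception that the blinding statement does not declare

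*Protocol article*

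**What the plan says.** All places are in the protocol article.

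- **Secondary outcomes:** "Falls will be tracked by research assistants during their daily visits". For the period after discharge, falls "will also be assessed by self-report at the one-month follow up time point after hospital discharge".
- **Intervention group:** research assistants "will visit each patient in the morning and afternoon/evening every day during hospitalization". They set the step goal, check progress, give feedback and help the patient to move.
- **Control group:** "The control group will receive brief visits from the research assistants conducting the intervention at the same time they went into the unit". These visits consist of less than five minutes of small talk. Dummy white boards are placed in the control rooms so that the researchers who do the health assessments cannot infer the arm.
- **Randomization and blinding:** "The primary investigator and data collection assessors are blinded to participant group assignment". No outcome is exempted.
- **Background:** the barriers to upright time are listed as "including fall concerns, pain, and lack of patient motivation". The stated overall objective includes that the intervention be safe.
- **Statistical analysis:** daily data go to mixed models for repeated measures, and other secondary outcomes go to a t-test or chi-square test. Falls are not named in either clause.

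**The concern.** The person who records whether an inpatient fell is the person who set that patient's step goal and may have walked with them. That person cannot be blind, and the white boards do not help, because they hide the arm from a different group of staff. A reader of the blinding section would assume that falls are ascertained blind.

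This matters more for falls than for most secondary outcomes. The trial encourages frail inpatients to move more, the article itself lists fear of falling as a barrier, and falls are the only listed outcome that plainly speaks to safety. Bias could run either way. An assistant who is present for walks may see or hear of more falls in the intervention arm, while one with a stake in the intervention may record fewer or classify a near-fall differently. With neither direction excluded, a reassuring result and an alarming one are both open to question.

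A smaller matter concerns the denominator. If falls are compared per patient, an arm with shorter stays has less time in which to fall.

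**Working it through.** **1. Who records falls, and do they know the arm?**

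| Step | Where it stands | What follows |
|---|---|---|
| In-hospital falls are noted at daily visits by research assistants | Secondary outcomes | The recorder is the daily visitor |
| Intervention visits set and check step goals | Intervention group | The visitor knows that this patient is in the intervention arm |
| Control visits are made by the same intervention staff, without goals | Control group | The visitor knows that this patient is in the control arm |
| Data collection assessors are blinded, no exception given | Randomization and blinding | Not true of whoever records in-hospital falls |
| Dummy white boards blind the health-assessment researchers | Control group | Protects other staff, not the visitors |

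The first three rows settle the question: in-hospital falls are recorded with knowledge of the arm. No arithmetic can size the resulting bias, because the article gives no fall rate and no rate of misrecording.

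**2. Days at risk.**

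The article states no figure for falls, so there is none to reproduce. Its only computed figure, 80% power for 62% versus 93% with 25 per arm, concerns the frailty index. It reproduces (80.7%, unpooled normal approximation, two-sided 5% level assumed), and this point does not depend on it.

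Inputs:
- 1.7 days: shorter stay associated with walking outside the room in an observational study cited in the Background.
- 18 days: mean stay in an acute geriatric trial cited in the Background, used here only as an illustration.
- 25 patients per arm: Sample size.
- Fall rate of 3 to 10 per 1000 patient-days, constant over the stay: my assumption, not in the article.

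Exposure lost: 1.7/18 = 9.4%, leaving 18 − 1.7 = 16.3 days.

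Daily rate ratio that would look like no difference per patient: 18/16.3 = 1.10. For a 14-day stay it is 14/12.3 = 1.14, and for a 28-day stay 28/26.3 = 1.07.

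Proportion with at least one fall at an equal daily rate, P = 1 − exp(−rate × days):

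| Rate per 1000 days | 18 days | 16.3 days | Patients with a fall per 25 |
|---|---|---|---|
| 3 | 5.3% | 4.8% | 1.31 vs 1.19 |
| 10 | 16.5% | 15.0% | 4.12 vs 3.76 |

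The shift is about 0.1 to 0.4 patients per arm.

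Comparison with chance: 25 × 18 = 450 patient-days give 450 × 0.003 = 1.35 to 450 × 0.010 = 4.5 expected falls per arm. Where the hidden rate ratio exactly offsets the shorter stay, both arms have that count. The standard error of the log rate ratio is then √(2/1.35) = 1.22 down to √(2/4.5) = 0.67. The masked effect is ln(1.10) ≈ 0.10, so it is 0.10/1.22 = 0.08 to 0.10/0.67 = 0.15 of one standard error.

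**The case against.** **The blinding statement may be meant more narrowly.** Read together with the white-board sentence, the blinded assessors can be taken to be the health-assessment researchers only, and the article does not hide that the visitors deliver the intervention. That reading is fair. It turns a strict contradiction into an undeclared exception, but falls are still recorded unblinded and the blinding section still does not say so.

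**Contact is matched.** Control visits take place at the same times and are made by the same staff, so the occasions to ask about falls are balanced by design. This stands. What differs is the content of the visit and the recorder's knowledge of the arm.

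**The source of the log is not stated.** The assistants may draw on charts or ward staff. That is possible, but the article says only that they track falls at their visits.

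**Incident reports are not blind either.** Unit staff can see patients being walked. This also stands: the remedy reduces the problem without removing it.

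**Stronger readings that a reader might infer.** One is that falls will be compared per patient. The article never assigns falls to a test, and the daily-data clause, whose model is said to handle unequal numbers of observations, could cover them. Another is that the trial expects shorter stays. Length of stay is an outcome, but no reduction is predicted, and the 1.7 days is an observational association. Nothing in the article supports a much larger shortening. Also, unequal exposure arises only in hospital. With the fixed month after discharge added, the difference would be about 1.7/(18 + 30) = 3.5%. Finally, taking readmissions by self-report, "Hospital readmissions within 30 days will be quantified by self-report at the one-month follow up time point after hospital discharge", is a choice of data source and not part of this inconsistency.

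**Conclusion.** The point holds in this form. In-hospital falls are ascertained by staff who know the arm and deliver the intervention, while the blinding section claims blinded data collection without qualification. This follows from the article's text alone and rests on no numerical assumption. Its effect on the fall comparison has unknown size and unknown sign. It does not touch the frailty or activity outcomes, but it weakens any statement about safety that relies on falls.

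The days-at-risk issue is secondary and conditional. It arises only if falls come under the t-test/chi-square clause and stays differ between arms. On a 1.7-day difference from an 18-day stay it would conceal a daily rate about 10% higher (7% to 14% for stays of 28 to 14 days). At the assumed 3 to 10 falls per 1000 patient-days that is well below chance variation with 25 per arm. It is a reason to report a rate, not a threat to the trial.

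**What to change.** 1. **Source.** Take in-hospital falls in both arms from the unit's incident reports and charts, abstracted by the assessors who are already blinded, under one written definition of a fall. Keep the assistants' log as a supplement, labelled as unblinded.
2. **Wording.** Amend the Randomization and blinding section to say that the visiting research assistants are unblinded, and which outcomes are assessed blind.
3. **Analysis.** Name falls in the Statistical analysis section. Report in-hospital falls as a rate per patient-day by arm, using a Poisson model with log days in hospital as offset, and report post-discharge falls separately over their fixed month. With the few falls expected, the interval will be wide and should be presented as such.

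**Cost.** Chart abstraction for 50 patients and a text amendment. Access to the records must be covered by consent. Unit staff who file the reports may not be blind, so some ascertainment bias could remain and should be acknowledged. The article reports that recruitment is ongoing, and charts of patients already enrolled can be abstracted afterwards if their consent allows it.

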### Statistical analysis

Data collected daily (e.g., physical activity outcomes) or weekly/monthly (e.g., frailty index) will be compared between the intervention and the control group using mixed-models for repeated measures. This modelling accounts for the differences in number of observations between participants, with variability in the number of total days of valid physical activity outcomes. A Chi-Square test of independence will be used to compare the proportion of patients who improve their frailty index scores by ≥ 0.10 or ≥ 0.03 in the intervention and control group at hospital discharge. Measurements conducted at admission and discharge only (e.g., comprehensive geriatric assessment) will be examined via a group by timepoint repeated measures or Friedman’s analysis of variance. Other secondary outcomes (e.g., length of hospital) will be analyzed between the intervention and control groups via independent samples *t*-test and Chi-square tests for continuous and categorical outcomes, respectively.

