### Sample size

We will recruit 25 participants for the usual care group and 25 participants for the treatment group. This number is based on a previous observational study in which 62% of individuals had an improvement of ≥ 0.10 in their frailty index score during hospitalization (see below for details) [8]. Using these prior estimates, group sample sizes of 25 per group achieves 80% power to detect a relative increase of 50% (i.e., an increase from 62 to 93%) in the proportion achieving a difference of 0.10 in the frailty index. A increase of 0.10 in the frailty index score has been shown to be associated with various adverse health outcomes including extended length of hospital stay, institutionalization, in-hospital falls, delirium, pressure ulcer incidence, and mortality [18].

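### Randomisation is stratified by pre-admission mobility, but the named two-group tests ignore it, and the admission/discharge scales get a valid but less efficient change-score comparison

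*Protocol article*

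**What the plan says.** **Design.** The Randomization and blinding section allocates patients "using an n = 6 block design and stratification by participants’ maximum level of mobility at pre-admission". The three levels are walking independently, needing a walking aid, and needing another person's help. The Sample size section sets 25 patients per group.

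**Responder outcome.** The Sample size section rests on an earlier study in which "62% of individuals had an improvement of ≥ 0.10 in their frailty index score during hospitalization", and on a rise to 93% with the intervention. The Frailty index section defines the outcome as "the proportion of patients whose frailty index changes by 0.03 and 0.10 from admission to discharge". The Statistical analysis section names the test: "A Chi-Square test of independence will be used to compare the proportion of patients who improve their frailty index scores" by at least 0.10 or 0.03 at discharge.

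**Other outcomes.** Scales taken only at admission and discharge, such as the Comprehensive Geriatric Assessment, get a group-by-timepoint repeated-measures analysis or Friedman's analysis of variance. Other secondary outcomes, length of stay among them, "will be analyzed between the intervention and control groups via independent samples" t-tests, or chi-square tests if categorical. Daily activity and the repeated frailty index go to mixed models for repeated measures, with no covariates listed.

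No section says that mobility enters any analysis.

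**The concern.** Stratified blocks keep the arms close to balanced on mobility, so mobility adds little to the variance of the treatment difference. A test that ignores the strata still counts the between-stratum variance in its standard error. If mobility predicts the outcome, that standard error is too large, the true type I error falls below 5%, and some power is lost. Mobility plausibly matters: it is the only stratification factor, and the frailty questionnaire itself has mobility and daily-living items.

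The second part concerns the admission/discharge scales. With two timepoints and complete data, the group-by-timepoint interaction in a repeated-measures analysis is the same test as a t-test on change. Its size is correct, but it uses the admission value less efficiently than a regression adjustment does. With 25 patients per arm, precision is scarce, and both the mobility level and the admission value are already collected.

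**Working it through.** **1. The plan's own figure.** Inputs from the Sample size section: 25 per group, 62% against 93%. Two-sided alpha of 0.05 is assumed, since the article states none.
- Arcsine: h = 2·asin(√0.93) − 2·asin(√0.62) = 0.793. Power = Φ(0.793·√(25/2) − 1.96) = Φ(0.843) = 80.0%.
- Unpooled normal: SE = √(0.62·0.38/25 + 0.93·0.07/25) = 0.1097. Power = Φ(0.31/0.1097 − 1.96) = 80.7%.
- Exact enumeration of the uncorrected chi-square test: 80.6%.

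The stated 80% reproduces.

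**2. Admission/discharge scales.** With equal variance σ² at both times and correlation r, a change score has variance 2σ²(1−r) and the ANCOVA residual has variance σ²(1−r²). The ratio is (1+r)/2. The article gives no r, so 0.5 to 0.7 is assumed. The effect is set at 0.81 SD of the change score, which gives the change-score test about 80% power. Its noncentrality is 0.81·√(25/2) = 2.864, and ANCOVA's is 2.864/√((1+r)/2). Power comes from the noncentral t distribution (48 df for change, 47 for ANCOVA on the admission value alone).

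| Analysis | Variance ratio | Noncentrality | Power |
|---|---|---|---|
| Change score | 1 | 2.864 | 80.1% |
| ANCOVA, r = 0.5 | 0.75 | 3.307 | 89.9% |
| ANCOVA, r = 0.6 | 0.80 | 3.202 | 88.0% |
| ANCOVA, r = 0.7 | 0.85 | 3.106 | 86.0% |

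Simulation of 50 patients (blocks of 6 in three strata, mobility assumed to explain 15% of variance) agrees. The change score has about 80 to 81% power. ANCOVA with mobility has 88 to 89%, 87 to 88% and 85% at r = 0.5, 0.6 and 0.7. At r = 0.6, ANCOVA without mobility already reaches 86%, so nearly all of the gain comes from the admission value. The simulated size of the change-score test is about 5%.

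**3. Responder test.** Simulation with 50 patients, assumed stratum shares of 30/40/30%, blocks of 6, overall rates held at 62% and 93%, and 8,000 runs per scenario. The step is the assumed log-odds difference between adjacent mobility levels. CMH is the Cochran-Mantel-Haenszel test stratified by mobility.

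| Step | Type I error, chi-square | Type I error, CMH | Power, chi-square | Power, CMH |
|---|---|---|---|---|
| 0 | 6.2% | 5.4% | 80.5% | 78.9% |
| 0.5 | 5.4% | 4.9% | 80.7% | 79.7% |
| 1.0 | 4.4% | 4.9% | 81.8% | 82.1% |
| 1.5 | 3.6% | 5.3% | 82.2% | 85.0% |
| 2.0 | 2.5% | 5.2% | 82.4% | 87.6% |

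The change in power runs from 78.9 − 80.5 = −1.6 points to 87.6 − 82.4 = +5.2 points. The plain test is conservative only from a step of about 1 upward. For scale, a step of 1 means response rates of 83%, 64% and 39% across the three levels under the null.

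**4. Length of stay.** If mobility explains a share R² of variance and is balanced by design, the unadjusted standard error is too large by 1/√(1−R²). The true size of a nominal 5% test is then about 2·(1 − Φ(1.96/√(1−R²))).

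| Assumed R² | SE ratio | True size |
|---|---|---|
| 0 | 1.00 | 5.0% |
| 5% | 1.03 | 4.4% |
| 10% | 1.05 | 3.9% |
| 20% | 1.12 | 2.8% |

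**5. Room for covariates in the responder model.** Expected non-responders at the design rates: 25·0.38 + 25·0.07 = 9.5 + 1.75 = 11.25. The chance of none in the intervention arm is 0.93^25 = 16%.

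**The case against.** The strongest reply is that nothing here is invalid. A chi-square test or t-test under stratified randomisation errs, if at all, on the safe side, and a change-score analysis has correct size. That stands, and so do these limits on the point:

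- A reader might infer that the plan ignores the admission value. It does not. The responder outcome is a change from admission, and the group-by-timepoint analysis includes admission as a timepoint. What the named tests lack is adjustment for it.
- A reader might infer that the planned tests are conservative throughout. The change-score analysis is not. The chi-square test is conservative only if mobility is strongly prognostic, and with weak or no prognostic effect stratifying loses up to 2 points of power.
- One could show a much larger loss by testing the discharge value of a scale with an unadjusted t-test (64% power in the r = 0.6 setting). The article does not plan that analysis, so the figure does not count against it.
- A reader might infer that the mixed models omit mobility or the admission value. The article lists no covariates for them, and such a list is commonly left to an analysis plan, which is not shown here.
- Nothing in the article says how strongly mobility predicts frailty change or length of stay.

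The reply does not dispose of the point, because the tests themselves are fixed in the text. A plain chi-square test of independence and an independent-samples t-test cannot carry the stratum, so an analysis plan that stratified them would depart from the article.

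**Conclusion.** The point holds as a cheap improvement in efficiency, not as an error of validity. The firmest part concerns the admission/discharge scales, where adjusting for the admission value cuts the variance to 0.75 to 0.85 of the change-score variance and lifts power from about 80% to about 85 to 90%. This rests on an assumed r of 0.5 to 0.7, equal variances at the two times and an effect of 0.81 SD of change.

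For the responder test, the outcome that sizes the trial, the case is weaker. Stratifying changes power by about -2 to +5 points over log-odds steps of 0 to 2. The plain test's true size falls from 4.4% to 2.5% over steps of 1 to 2, and it is not conservative below that. For length of stay the direction is the same, and its size depends on an unknown R². The stratum shares and prognostic strengths are all assumptions. The stated 80% power is right for the test named.

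**What to change.** Revise the Statistical analysis section before unblinding:

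1. **Admission/discharge scales:** ANCOVA of the discharge value on the admission value, treatment group and mobility level, in place of the group-by-timepoint analysis.
2. **Responder proportions (0.10 and 0.03):** Cochran-Mantel-Haenszel test stratified by mobility level, in place of the plain chi-square test.
3. **Length of stay:** include mobility level as a covariate.
4. **Mixed models:** state whether mobility and the admission value are covariates, or refer to the analysis plan. This is a clarification only.

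Logistic regression with several covariates should not be the main responder analysis. With about 11 non-responders expected, treatment, the admission index and two mobility terms leave fewer than 3 non-responders per coefficient (11.25/4 = 2.8). The 16% chance of an intervention arm with no non-responders would also leave the treatment effect without a finite estimate.

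The cost is a change of text, a few degrees of freedom, and up to 2 points of power on the responder test if mobility turns out not to be prognostic. A sparse mobility level may need merging with its neighbour, and the merging rule should be written down in advance. No extra patients or data are needed, since mobility is already recorded for randomisation.

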Frailty is a useful outcome measure of overall health state in acute care and is a predictor of adverse health outcomes [13]. However, few interventional studies have measured frailty as an outcome in hospitalized adults [14]. During a randomized clinical trial, two daily sessions of moderate-intensity exercises improved the frailty levels of hospitalized older adults more than the control group [15]. In another study in acute geriatric care, researchers did not observe changes in frailty between the intervention and control groups in those who did, on average, ~five, ~ 20 min sessions of functional exercise sessions over an average of 18 days hospital stay [16]. Perhaps, more frequent patient contact and/or targeting overall physical activity in the absence of periodic structured exercise but combined with goal setting and feedback on performance may be a more feasible approach to helping inpatients move more. The use of goal setting in hospital has been shown to be independently associated with increased physical activity [17]. Our proposed study will strengthen the evidence base of movement and frailty in healthcare by examining whether a step-count based intervention during a patients’ stay in acute care is successful and reduces the level of frailty during hospitalization. Such an understanding is vital to provide guidance on best evidence practice in reducing excessive bed rest in acute care.

The overarching objective of our ***Breaking Bad Rest*** clinical trial is to provide a safe, feasible, and effective intervention that improves the health of inpatients. Using a novel intervention design that involves frequent patient visits, goal setting, and feedback on performance we will determine the feasibility of our ***Breaking Bad Rest*** intervention model in acute geriatric care. We will test the hypothesis that our intervention will improve physical activity and frailty levels and health outcomes to a greater extent than usual care during hospitalization.

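### Friedman's test, named as the alternative analysis for outcomes measured only at admission and discharge, has no treatment-group term and cannot compare the arms

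*Protocol article*

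**What the plan says.** The Statistical analysis section of the protocol article groups outcomes by how often they are measured. For the class "Measurements conducted at admission and discharge only (e.g., comprehensive geriatric assessment"), it states that they "will be examined via a group by timepoint repeated measures or Friedman’s analysis of variance". It gives no other test for this class.

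Two instruments described under Secondary outcomes fall into it. For the first, "A physician or trained researcher will conduct this Comprehensive Geriatric Assessment upon admission and discharge", and a frailty index is to be derived from it. The second, the Pictorial Fit-to-Frail Scale, is completed "on admission and prior to discharge". Each therefore has two timepoints in hospital.

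The hypothesis at the end of the Background is comparative: that "our intervention will improve physical activity and frailty levels and health outcomes to a greater extent than usual care during hospitalization".

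**The concern.** The sentence offers Friedman's test as a substitute for a group-by-timepoint analysis, presumably for data that do not suit the parametric model. It is not the rank counterpart of that analysis. It is a one-way, within-patient test that asks whether values differ across timepoints. It has no between-group factor and no group-by-time interaction.

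Two of the trial's supporting frailty measures could therefore end up with a test that does not address the hypothesis. Change over time is expected in a recovering inpatient population whichever arm a patient is in, so a significant result would carry no information about the intervention. A true difference between arms could also go unseen.

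**Working it through.** **1. What the statistic contains.** Friedman's test ranks each patient's own values across the repeated conditions. With two timepoints and no ties, let n+ patients improve and n− worsen, with n = n+ + n−. The statistic reduces to

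Q = (n+ − n−)² / n, on 1 degree of freedom,

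which is the sign test of admission against discharge. Treatment group does not appear in it. Swapping every arm label leaves the pooled Q unchanged, so no group effect or interaction can be tested. This step needs no assumption about the data.

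**2. Inputs for the illustration.**
- Group sizes, from Sample size: "We will recruit 25 participants for the usual care group and 25 participants for the treatment group".
- Two-sided 5% level: assumed, because the article states none.
- No treatment effect, no tied values, and a common probability p of improving of 0.70, 0.75 or 0.80 in both arms: assumed, because the article gives no such figure for these two instruments.

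The article's own design figure (80% power for "an increase from 62 to 93" per cent) concerns a different outcome and does not enter here. It does reproduce: exact enumeration of the uncorrected chi-square test with 25 per arm gives 80.6%.

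**3. Pooled test, n = 50.** The exact two-sided sign test rejects when the number improving is at most 17 or at least 33. With X ~ Binomial(50, p), the rejection probability is P(X ≤ 17) + P(X ≥ 33).

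| p improving in both arms | Exact sign test | Usual chi-square form (rejects at ≤ 18 or ≥ 32) |
|---|---|---|
| 0.70 | 78% | 86% |
| 0.75 | 94.5% | 97.1% |
| 0.80 | 99% | 99.7% |

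Every one of these rejections occurs with no difference between the arms.

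**4. Separate tests, n = 25 per arm.** The exact test rejects at ≤ 7 or ≥ 18 improving. Let r be the rejection probability in one arm. The arms are independent, so exactly one is significant with probability 2r(1 − r), and only the intervention arm with probability r(1 − r).

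| p | r | Exactly one arm significant | Intervention arm only |
|---|---|---|---|
| 0.70 | 0.512 | 2 × 0.512 × 0.488 = 50% | 25% |
| 0.75 | 0.727 | 2 × 0.727 × 0.273 = 40% | 20% |
| 0.80 | 0.891 | 2 × 0.891 × 0.109 = 19% | 10% |

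**5. Comparison with between-group tests, by simulation.** The setting is 25 per arm, normal data with SD 1, an assumed admission–discharge correlation of 0.6, and 4,000 runs per scenario.

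| Scenario | Pooled Friedman rejects | Mann-Whitney on change | t-test on change (equals the group-by-time interaction) |
|---|---|---|---|
| Both arms improve by 0.5 SD (no group difference) | 89.8% | 3.8% | 4.7% |
| Arms move 0.4 SD in opposite directions | 5.2% | 85.3% | 87.9% |

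Pooled Friedman rejects often when the arms do not differ. It stays near 5% when they differ strongly. Both between-group tests behave as they should.

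**The case against.** The best reply is that the sentence names two methods joined by *or*, and the first is sound. With two timepoints the group-by-timepoint interaction is equivalent to a t-test on the change score and answers the trial's question directly. That stands, so the consequence is conditional on the Friedman branch being used. A reader might infer that these outcomes cannot answer the trial question at all. The text does not support that.

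A reader might also infer that the Friedman branch is the likely one because these scales will be judged non-normal. The article gives no distribution for either instrument and no rule for choosing the branch. Such a rule may properly sit in an analysis plan that is not shown, so no likelihood can be claimed.

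Nor does the article say that the test would be run arm by arm, or that a pooled time effect would be reported as a treatment effect. The calculations show what the test would do in either use. They do not show that the investigators intend that reading.

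Finally, the scope is narrow. The repeated frailty index and activity outcomes are compared between arms by mixed models, the proportions improving by 0.10 or 0.03 by chi-square, and the other secondary outcomes by t-test or chi-square. All of these are between-group analyses.

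The structural point survives. The objection that details may be left to an analysis plan covers omissions. Here the published text names a specific test that cannot do the job of the analysis it stands in for, and nothing else in the article supplies a between-group rank test for these outcomes.

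**Conclusion.** Wrong as written, with limited reach. That Friedman's test lacks a group term is certain and rests on no assumption. If that branch is used, the Comprehensive Geriatric Assessment frailty index and the Pictorial Fit-to-Frail Scale have no valid between-group comparison.

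The percentages are illustrative. They rest on assumed improvement rates of 70% to 80%, no ties, no treatment effect and a two-sided 5% level, and they would shift with other inputs. The simulation also depends on its assumed normality and correlation.

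The point ranks below a must-fix because only secondary outcomes measured at admission and discharge are affected. The trial's main frailty and activity conclusions do not depend on it.

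**What to change.** In the Statistical analysis section, replace Friedman's test with a between-group rank method for outcomes measured only at admission and discharge. Either of these would serve:
- rank ANCOVA of the discharge value, adjusted for the admission value and the pre-admission mobility stratum used in randomisation;
- a van Elteren test on the admission-to-discharge change, stratified by mobility level.

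The group-by-timepoint branch can stay. Optionally, ANCOVA of the discharge value adjusted for the admission value and mobility stratum could replace it for better precision, but that is a preference and not a correction.

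The cost is one sentence of analysis text, with no new data and no change to assessments. The article reports recruitment as ongoing, so the change is best made before unblinding, so that the choice of test is not made after seeing results.
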